### Objectives

To investigate whether commonly prescribed medications, previously identified as potentially cerebroprotective, are associated with the incidence or progression of neurodegenerative disease.

We will focus on the following medications:
Treatments for hypertension.Treatments for hypercholesterolaemia.Treatments for type 2 diabetes.

Along with the following neurodegenerative diseases:
Alzheimer's disease (AD).Non-Alzheimer's disease dementias (NADD).Parkinson's disease (PD).Amyotrophic lateral sclerosis (ALS).

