### Sample selection

We will investigate the incidence and progression of AD, NADD, PD and ALS. Our investigations into the incidence will focus on treatments which are reported to be cerebroprotective and are currently prescribed for hypertension,^6^ hypercholesterolaemia^7^
^8^ and type 2 diabetes.^9^ For each treatment, we will conduct two analyses. The first will compare treated to untreated individuals with similar indications—this is cohort A. The second will compare the outcomes of individuals given different subclasses of specific medications—this is cohort B. We will also investigate progression using a third cohort, cohort C. Progression will be defined as the postdiagnosis survival of a patient. For each neurodegenerative disease group of interest, we will determine the effects on progression of the three possible new treatments. In cohort C, exposure will be defined in two ways: (1) using patients being prescribed these drugs at the time of diagnosis of their neurodegenerative disease; and (2) using those issued new prescriptions postdiagnosis. The structure of these three cohorts is summarised in table 1 and further explained in the text that follows. All of the cohorts rely on defined diagnoses and exposures, which are recorded in the CPRD through the use of Read and product codes, respectively. Read codes uniquely identify clinical terms recorded by the general practitioner (GP) during a consultation, while product codes uniquely identify prescriptions issued. Both types of code are recorded with a date, and this will be used to determine the dates of diagnosis and exposure required to define the cohorts.

**Table 1 BMJOPEN2016012044TB1:** Comparison of the three cohort types

	Cohort A	Cohort B	Cohort C
Purpose	To investigate incidence by comparing treated and untreated individuals.	To investigate incidence by comparing the different drug subclasses of each treatment.	To investigate progression by comparing treated and untreated individuals.
Number of cohorts required	There will be three cohorts of this type, one for each treatment of interest.	There will be three cohorts of this type, one for each treatment of interest.	There will be three cohorts of this type, one for each of dementia (AD or NADD), PD and ALS.
Exposures	Treatments for hypertension, hypercholesterolaemia and type 2 diabetes.	Treatments for hypertension, hypercholesterolaemia and type 2 diabetes.	Treatments for hypertension, hypercholesterolaemia, and type 2 diabetes.

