Start of follow-up (index date)	Date at first risk of the condition the treatment is used for or date of first diagnosis of the condition itself if there was no preceding period ‘at risk’.	Date of first prescription of a treatment of interest.	Date of first diagnosis of neurodegenerative disease of interest.
Outcome	Diagnosis of neurodegenerative disease of interest.	Diagnosis of neurodegenerative disease of interest.	Death.
Exclusion criteria	Individuals with <12 consecutive months of records prior to cohort entry.	Individuals prescribed treatment and control medications at the same time or with <12 consecutive months of records prior to cohort entry.	Individuals with <12 consecutive months of records prior to cohort entry.
Statistical analysis	Conventional regression, propensity score regression, instrumental variable analysis and marginal structural models.	Conventional regression, propensity score regression, instrumental variable analysis and marginal structural models.	Conventional regression, propensity score regression and marginal structural models.

AD, Alzheimer's disease; ALS, amyotrophic lateral sclerosis; NADD, Non-Alzheimer's disease dementias; PD, Parkinson's disease.

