#### Cohort C

For each neurodegenerative disease group of interest, we will create a cohort of individuals with a read code indicating this outcome (see online supplementary file 4) or a product code indicating they received treatment for the outcome (see online supplementary file 5). These cohorts will be used to investigate the associations of neurodegenerative disease progression with exposure to one of the three treatment groups of interest: treatments for hypertension, treatments for hypercholesterolaemia and treatments for type 2 diabetes. We will investigate both exposure before and after the diagnosis of a neurodegenerative disease. For all of the treatments we consider, each cohort will be split into ‘exposed’ and ‘unexposed’ groups. In the analysis, individuals in the ‘exposed’ group, that is, those who were prescribed the treatment under investigation, will be compared with individuals in the ‘unexposed’ groups, that is, those who did not receive the treatment.

10.1136/bmjopen-2016-012044.supp4supplementary file

10.1136/bmjopen-2016-012044.supp5supplementary file

Follow-up for cohort C will start with the first recorded read code indicating AD or other neurodegenerative disease (see online supplementary file 4) or, in the absence of a diagnosis, the first recorded product code indicating they received treatment for a neurodegenerative disease (see online supplementary file 5). Follow-up will end with the earliest of death or censoring due to the end of registration at a CPRD general practice.

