### Bias

There are three main sources of bias in our results: ascertainment bias, collider bias and immortal time bias. To overcome ascertainment bias, we will control for consultation rate in our analyses because people who have more chronic conditions such as hypertension, diabetes or renal insufficiency may have higher rates of consultation, which may also increase the opportunity for recording other diagnoses such as dementia. Collider bias could occur if we conditioned on events that happened as a result of the prescription the patient was issued. To prevent this form of bias from affecting our results, we will define each covariate using data inputted prior to the index date.^14^ Finally, we will minimise the risk of immortal time bias in two ways. First, to prevent misclassified immortal time, we will define exposures based on the first prescription observed in the database^10^ and use an intention-to-treat analysis. Second, to minimise immortal time, we will follow-up patients (exposed and unexposed) from a consistent index date. This will be a test result or a read code indicating diagnosis where possible;^15^ however, to capture all relevant patients, we will allow those receiving treatment without a recorded diagnosis to be included.

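### Taking covariates before the index date does not prevent collider bias in cohort C exposure definition (1), where entry depends on a diagnosis that follows the prescription

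*Protocol article*

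**What the plan says.** All references are to the protocol article.

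- **Bias** defines the problem: "Collider bias could occur if we conditioned on events that happened as a result of the prescription the patient was issued". The only remedy offered is the timing of covariates: "To prevent this form of bias from affecting our results, we will define each covariate using data inputted prior to the index date".
- **Cohort C** fixes entry: "we will create a cohort of individuals with a read code indicating this outcome", or a product code for treatment of the disease. Table 1 gives the start of follow-up as "Date of first diagnosis of neurodegenerative disease of interest".
- **Sample selection** gives two exposure definitions for cohort C. Definition (1) is "using patients being prescribed these drugs at the time of diagnosis of their neurodegenerative disease"; definition (2) is a new prescription issued after diagnosis. The Cohort C section confirms both: "We will investigate both exposure before and after the diagnosis of a neurodegenerative disease".
- **Sample selection** also sets the outcome: "Progression will be defined as the postdiagnosis survival of a patient".
- **Objectives** asks whether the drugs "are associated with the incidence or progression of neurodegenerative disease". An effect on diagnosis is thus one of the hypotheses under test.

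**The concern.** On the plan's own definition, a diagnosis made after a prescription is an event that may result from it. Cohort C consists only of people who had that event. Under definition (1), restricting to them is itself conditioning of the kind the Bias section warns about, and a rule on covariate dates does not act on who enters the cohort.

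If a drug prevents or delays some diagnoses, or keeps more people alive long enough to be diagnosed, treated and untreated cases can differ at entry in frailty or pathology that is not recorded. A drug with no effect after diagnosis could then show a difference in survival, in either direction. A reader who accepts the Bias section would take that difference as free of this problem.

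**Working it through.** **1. Order of events in cohort C**

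| | Definition (1) | Definition (2) |
|---|---|---|
| Prescription relative to diagnosis | before | after |
| Can diagnosis be a result of the prescription? | yes, by the study's hypothesis | no |
| Are pre-index covariates also pre-prescription? | not necessarily | yes |

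The third row is a second gap. The Covariates section adjusts for coronary disease, bypass surgery and cerebrovascular disease including stroke. For someone already taking an antihypertensive or a statin, these can occur after treatment start and before diagnosis, and so count as pre-index.

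**2. Is there another safeguard?** Table 1 lists no instrumental variable analysis for cohort C. The Marginal structural models section builds its weights on observed characteristics, and Statistical methods says such models assume no unmeasured confounders. The Covariates section concedes that some variables, such as exercise, are not recorded. Nothing else addresses selection on diagnosis.

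**3. Size.** The plan gives no figure to reproduce, and every input in this step is an assumption. The drug has no effect on death after diagnosis throughout.

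*(a) Unmeasured binary factor.* The factor has 30% prevalence, is independent of the drug before diagnosis, multiplies diagnosis by 4 and multiplies death by 3. The drug ratio on diagnosis is 0.7. Let q be the share of diagnosed patients who carry the factor. The false mortality ratio is (1+2q₁)/(1+2q₀), with q₁ for treated and q₀ for untreated.

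- Exactly multiplicative risks: q₁ = q₀ = 0.632, ratio 1.000.
- Additive risks: q₀ = 0.3×4/(0.3×4+0.7×1) = 0.632; q₁ = 0.3×3.7/(0.3×3.7+0.7×0.7) = 0.694; ratio 2.388/2.263 = 1.055.
- Logistic, baseline risk 20%: q₁ = 0.542, q₀ = 0.517, ratio 1.025.
- Proportional hazards, baseline cumulative hazard 0.2: q₁ = 0.584, q₀ = 0.566, ratio 1.018.
- If the drug does not affect diagnosis, the ratio is 1.000 in every model.

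Weaker inputs (drug ratio 0.8 or 0.9, factor 2 or 3 on diagnosis, 1.5 or 2 on death) give smaller values.

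*(b) Case mix.* A poorer-prognosis component makes up a share v of cases and has death ratio h; the drug reduces only that component, by relative risk RR. Then v′ = v·RR/(v·RR+1−v) and the false HR is (1+(h−1)v′)/(1+(h−1)v).

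- v = 0.3, RR = 0.5, h = 2: v′ = 0.15/0.85 = 0.176; HR = 1.176/1.3 = 0.905.
- v = 0.2, RR = 0.7, h = 1.5: v′ = 0.14/0.94 = 0.149; HR = 1.074/1.1 = 0.977.

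This route is relevant because cohort C pools AD with other dementias.

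*(c) Survival to diagnosis.* Simulation of 2 million people used Gompertz hazards, a shared normal frailty with SD 0.25 to 1.0, and stratification by age at diagnosis. A drug that only lowers death before diagnosis (HR 0.7 to 0.8) gave about 1.01 to 1.10. A drug that only lowers incidence (HR 0.6 to 0.8) gave about 1.01 to 1.04.

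**4. Yardstick.** Table 3 gives a detectable HR of 0.931 for dementia: 1−0.931 = 0.069, or about 7%; its inverse is 1/0.931 = 1.074. Table 3 shows neither deaths nor exposed share for cohort C, so 0.931 cannot be reproduced and serves only as a scale.

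**The case against.** The disputed sentence is about covariates, and for covariate conditioning in cohorts A and B and definition (2) it is sound. The Objectives section speaks of association, and the Covariates section already admits unmeasured confounding. This softens the point but does not remove it: the sentence claims prevention for the results without exception, and Sample selection speaks of effects on progression.

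A reader might infer that the bias is certainly present in the progression results. The document does not support that. Bias requires that the drug changes diagnosis or survival to it, that diagnosis or prior survival shares unadjusted causes with later death, and that the joint effect is not exactly multiplicative. Illustration (a) gives 1.000 when the drug leaves diagnosis unchanged or the effects are exactly multiplicative. The illustrations also adjust for less than the plan does; only frailty left over after the full covariate list matters.

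A reader might also infer that the drugs with the strongest incidence results have the most distorted progression results. That does not follow either. In the simulations the incidence route was the smaller one, and a drug acting only on death before diagnosis may show little in the cohort A hazard ratio.

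Finally, the Exposures section requires no related product in the 12 months before follow-up. Read literally, this removes established users from definition (1) and leaves little time for a drug to alter incidence. The Cohort C text points the other way, so this is an inconsistency that affects the size of the problem, not a refutation.

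**Conclusion.** The concern holds in a limited form. The property claimed in the Bias section is not secured for cohort C definition (1), for two reasons: entry depends on a possible consequence of the prescription, and pre-index covariates need not be pre-prescription. This selection bias is not prevented and may remain. Cohorts A and B and definition (2) do not share this particular problem.

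The size cannot be obtained from the document. Under assumed inputs and no drug effect after diagnosis, the false ratio runs from nil to roughly the 7% that the plan treats as detectable in dementia, with the most extreme inputs slightly beyond it (0.905 and 1.10). It can lie on either side of 1. The incidence route alone gave about 1.01 to 1.04 in simulation and at most 1.055 in closed form.

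**What to change.** - In the Bias section, restrict the claim of prevention to covariate conditioning in cohorts A and B and definition (2), and name selection on diagnosis as a limitation of definition (1).
- For definition (1), take covariates before the first prescription where records allow. Report the hazard ratio as an association among diagnosed patients, not as an effect on progression.
- Add a quantitative bias analysis over a range of drug effects on both diagnosis and death before diagnosis. Do not make it conditional on the cohort A hazard ratio: that would miss the pre-diagnosis-death route, and cohort A uses a different contrast (treatment within 6 months of the indication's diagnosis, among people with or at risk of that indication).
- Report definition (2) beside it as the analysis free of this selection. Because Table 1 starts cohort C follow-up at diagnosis, exposure must be time-varying or follow-up must start at the new prescription, to avoid immortal time. Whether definition (2) should be the sole basis for conclusions on progression is a trade-off, since it is likely to have fewer exposed patients.
- Reconcile the 12-month rule in Exposures with definition (1) in Sample selection.

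The cost is some rewording, a modest amount of extra analysis and a narrower claim from definition (1).

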### Confounding

We have identified two key sources of confounding in our study: confounding by indication and time-dependent confounding. To address the former, we will use four different statistical methods, which have different approaches for modelling confounding. Through examination of these approaches, we hope to highlight any uncontrolled confounding that may be leading to false conclusions about drug effect. We will also account for confounding by indication in the construction of our cohorts. Consider cohort A, where we compare ‘exposed’ and ‘unexposed’ groups of individuals. Drawing the ‘unexposed’ group from the full population can introduce bias as they are likely to be in better health. We will avoid this by defining cohort entry on the basis of first test or recording of a relevant read code so the ‘exposed’ and ‘unexposed’ groups will have more in common. In addition to this, we will address time-dependent confounding in our study. This will be carried out using marginal structural models, which can allow for time-dependent confounding and treatment switching between products.

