#### Covariates

We will match all covariates on date of birth, sex, year of index date and years of recorded history in the database before the index date. The covariates we will include in our analyses are body mass index, smoking status, alcohol consumption, a postcode-based measure of socioeconomic position, previous history of coronary-artery disease, previous coronary-bypass surgery and cerebrovascular disease including stroke. We will also control for other major chronic illness (including cancer, arthritis) using the Charlson Index^11^
^12^ and for consultation rate, calculated by dividing the total number of clinic visits prior to the index date by the length of each patient's follow-up. If there are missing data in the covariates, we will consider using multiple imputation. Unfortunately not all covariates of interest, such as exercise, are recorded within the CPRD, and this may lead to unmeasured confounding. We hope to minimise this confounding by using methods, such as instrumental variable analysis, which can account for it to some degree.

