### Statistical methods

We will use four statistical approaches in our study—they are multivariable adjusted Cox regression, propensity matched regression, instrumental variable analysis and marginal structural models. We are committed to presenting the findings from all our analyses, irrespective of the direction of findings and will handle discrepancies between them by assessing the merits of each method in the given situation. If we discover large main effects of specific medications, we may investigate interactions between covariates and will seek to replicate any interactions in other large samples.

We will be using an intention to treat analysis in our primary analysis. The reasons for this are twofold. First, while there are theoretical statistical models for estimating the effects of treatment switching such as marginal structural models, these methods require the strong assumption that there are no unmeasured confounders. Second, to the best of our knowledge there are no instrumental variable methods for estimating the effects of treatment switching. We will investigate treatment switching using marginal structural models in a secondary analysis. All of the methods we will use for this study are summarised below.

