#### Multivariable adjusted Cox regression

In our first analyses, a conventional observational analysis, we will estimate the HRs of incidence and survival using Cox proportional hazards models. Both analyses will use the actual prescriptions issued to the patients.^20^ We will report these associations adjusted for basic confounders (age and gender) and results adjusted for all measured covariates described previously. We will also perform tests of the proportional hazards assumption.

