#### Marginal structural models

In our fourth analysis, we will estimate the effects of each treatment using marginal structural models.^32^ We will use these models to account for time-dependent confounding and treatment switching. We will construct inverse probability weights for each treatment based on the patients' observed characteristics such as gender, age, comorbidities and concurrent treatments. We will use these models to estimate the odds and HRs of disease incidence and progression.

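### In cohort C, comparing the methods cannot reveal unmeasured confounding: the instrumental variable analysis is left out and the three remaining methods use recorded covariates only

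*Protocol article*

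**What the plan says.** The Confounding section sets out the strategy against confounding by indication: "To address the former, we will use four different statistical methods, which have different approaches for modelling confounding". It then gives the purpose of using several methods: "Through examination of these approaches, we hope to highlight any uncontrolled confounding that may be leading to false conclusions about drug effect". Neither statement is limited to particular cohorts. The abstract, the strengths and limitations list and the Statistical methods section also speak of four methods for the study as a whole.

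Table 1 (under Sample selection) divides the methods by cohort. Cohorts A and B have "Conventional regression, propensity score regression, instrumental variable analysis and marginal structural models". Cohort C has "Conventional regression, propensity score regression and marginal structural models". The article gives no reason for the omission and no substitute check.

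On unrecorded confounders, the Covariates section accepts that some variables, such as exercise, are not in the database, and continues: "We hope to minimise this confounding by using methods, such as instrumental variable analysis, which can account for it to some degree". No other method is named there. The Statistical methods section says of marginal structural models that "these methods require the strong assumption that there are no unmeasured confounders".

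**The concern.** A comparison of methods tells you about a source of bias only if the methods respond to it differently. In cohorts A and B, the instrumental variable analysis rests on an assumption different from that of the other three, so a gap between it and them could point to unmeasured confounding. In cohort C that contrast is gone, yet the general statement in the Confounding section still covers it.

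Cohort C also has the least protection by design. Cohort A requires patients to have, or be at risk of, the indication. Cohort B compares treated patients with other treated patients. Cohort C compares treated patients with everyone who has the neurodegenerative disease and did not receive the drug, whether or not they had the indication, and the outcome is death. All progression findings come from this cohort. A reader who sees three similar hazard ratios there, and has read the Confounding section, could take the similarity as reassurance that it does not provide.

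**Working it through.** **1. The plan's own figure.** The point rests on assumptions and on no stated figure. The only number used as a yardstick is the cohort C minimum detectable HR in table 3: 0.931 for dementia (N = 105 471), which is a reduction of 1 − 0.931 = 6.9%. It cannot be reproduced from the article, because neither the exposed share nor the number of deaths is given there. For scale, with two-sided α = 0.05, 80% power and equal groups, Schoenfeld's formula gives 4 × (1.960 + 0.842)² / (ln 0.931)² = about 6,142 deaths.

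**2. What each cohort C method adjusts for.**
- Cox regression: "results adjusted for all measured covariates described previously".
- Propensity matching: the score comes from a logistic regression of treatment on that same covariate list.
- Marginal structural models: "We will construct inverse probability weights for each treatment based on the patients' observed characteristics such as gender, age, comorbidities and concurrent treatments".

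An unrecorded common cause of prescribing and death enters none of the three. Each is biased by it, in the same direction.

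**3. Illustration with upward confounding.** The truth is HR = 1. There are two measured covariates L1 and L2 and one unmeasured standard-normal factor U:
- logit P(treated) = −1 + 0.4·L1 + 0.3·L2 + g·U
- hazard = 0.1 × exp(0.3·L1 + 0.2·L2 + g·U), follow-up cut at 5 years
- n = 40,000, 8 runs per setting, treatment fixed at baseline. Matching was 1:1 nearest neighbour without replacement, within common support and without a caliper.

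| g (assumed) | Adjusted Cox | Matched Cox | Weighted Cox | Largest gap between means |
|---|---|---|---|---|
| 0 | 1.003 | 1.003 | 1.001 | 0.002 |
| 0.3 | 1.094 | 1.092 | 1.092 | 0.002 |
| 0.6 | 1.353 | 1.346 | 1.349 | 0.007 |

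A value of g = 0.3 means an odds ratio for treatment, and a hazard ratio for death, of exp(0.3) = 1.35 per standard deviation of U.

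**4. Illustration with downward confounding.** The truth is HR = 1, with four measured covariates, 35% exposed and about 60% deaths (all assumed). U raises the log-odds of treatment by g and lowers the log-hazard by g. Matching used a caliper of 0.2 SD of the logit. At g = 0.3 the Cox, matched and weighted HRs were 0.92, 0.93 and 0.93; at g = 0.4 they were 0.87, 0.88 and 0.88. At g = 0.3 all three were significant together in 94% of runs at N = 20,686 (the Parkinson's disease cohort) and in 100% at N = 105,471 (the dementia cohort). The mean within-run gap between methods was 0.012 to 0.021 with the confounder, against 0.007 to 0.014 without it. That difference is too small to serve as a warning.

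**5. What the omitted method would add.** The setting is as in step 3, with n = 200,000 and a prescribing-preference instrument built from seven prior prescriptions and valid by construction. The true risk difference is 0. For g = 0, 0.3 and 0.6, ordinary regression gave 0.000, 0.025 and 0.087. The instrumental variable estimate gave 0.007, −0.002 and −0.004 (SD between runs about 0.008 to 0.014). The two separate as unmeasured confounding grows, whereas the three cohort C methods do not.

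**The case against.** The strongest reply is that the article promises less than a reader might infer. Several parts of it stand.

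- **A concordance rule.** One might read the plan as treating agreement between methods as proof of robustness. No section says so. The Confounding section expresses a hope, and the Statistical methods section deals only with disagreement, which is to be judged case by case, with all results presented.
- **Agreement under any confounding.** One might conclude that the three methods must agree however the result is confounded. That is too broad. The Confounding section speaks of uncontrolled confounding, which includes measured confounding that is poorly modelled or varies over time. Only the marginal structural model handles the time-varying part, together with switching, and matching changes the target population. The three can differ on all of these. Such differences would not diagnose an unrecorded confounder either.
- **The size of the bias.** The simulations use a treatment fixed at baseline and assumed effect sizes, while the planned marginal structural models address switching over time. The downward one also adds a caliper that the article does not specify, although the upward one uses none and shows the same pattern. That the bias at g = 0.3 lies near 0.931 reflects the chosen inputs.
- **Disclosure.** Table 1 shows the cohort C methods openly, the assumption behind marginal structural models is stated, and the instrumental variable analysis is said to help only in part. Some unrecorded health differences may be captured by the Charlson Index and the consultation rate. The Introduction says the findings will be used collectively to prioritise drugs, so cohort C does not act alone.

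What the reply does not remove is that the Confounding section assigns a task to the comparison of methods, makes no exception for cohort C, and in that cohort the comparison cannot do the part that concerns unrecorded confounders.

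**Conclusion.** The point holds for unmeasured confounding in cohort C. The general statement in the Confounding section and the cohort C column of table 1 do not fit together: the method whose disagreement could signal an unrecorded confounder is absent, and nothing replaces it. This conclusion follows from the stated methods and needs no simulation.

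The size is illustrative. With an unrecorded factor of log-scale strength 0.3 on both treatment and death, a null drug effect appears as a shift of about 7–9% in all three hazard ratios at once, comparable with the 6.9% reduction that the dementia cohort is meant to detect. The confounder strength, exposed share, death rate and baseline-only treatment are assumptions, so this is no estimate of the actual bias. Nor do the documents show that leaving out the instrumental variable analysis was wrong. There may be good reasons for it, and the repair does not depend on restoring it.

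**What to change.** 1. In the Confounding and Statistical methods sections, and in the matching sentences of the abstract and the strengths and limitations list, limit the four-method comparison to cohorts A and B.
2. State that agreement between the three cohort C methods is not evidence against unmeasured confounding.
3. Report an E-value or a quantitative bias analysis with each primary cohort C hazard ratio. With three disease cohorts, three drug groups and two exposure definitions, that is 3 × 3 × 2 = 18 hazard ratios under one primary model.
4. Where a cause of death that the drug class should plausibly not affect can be named in advance, add it as a negative-control outcome from the linked ONS data, as a supporting check. The article identifies no such cause, so this step is conditional.

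The first two changes are wording, and the third needs little computation. A negative control is more work: 18 models per outcome under one method, or 18 × 3 = 54 if all three methods are run. It will have fewer events and so a less precise estimate. The progression claims will also have to be worded more cautiously.
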